**Fig. 1 Fig1:**
[figure not shown]
Spaeth Richman Contrast Sensitivity Test (SPARCS). Two parallel horizontal lines and 2 parallel vertical lines intersect to create 9 boxes, including a 5 cm rectangle in the center. Note the darkened square waves in the right upper quadrant. During a “set”, darkened square waves randomly appear briefly in 1 of the 5 tested areas while the other 4 areas remain the same shade as the background. Contrast between the bars and background decreases by 50 % after each cycle

ADREV (assessment of disability related to vision) is a performance-based measure of vision related disability [16]. There are 9 items included in ADREV: 1) reading in reduced illumination 2) recognizing facial expression 3) detecting motion 4) reading signs at a distance 5) finding large and small objects spread around a room 6) navigating an obstacle course 7) putting a stick into holes of different sizes 8) telephone simulation and 9) matching socks. ADREV is the parent test for a newly modified performance-based assessment utilizing four of the original nine items. This instrument, the Compressed Assessment of Ability Related to Vision (CAARV), correlates excellently with the 9-item ADREV while only requiring between 10 and 15 min to complete (Table 2) [27]. The 4 CAARV items include: 1) computerized motion detection 2) recognizing facial expressions 3) reading street signs and 4) finding objects in a room. Patients complete CAARV sub-tests with both eyes open. They use their own appropriate refractive correction in order to simulate normal function. The patients complete two sub-tests in ambient lighting and two sub-tests in a dark room. Each item is scored from 0 to 7, 7 being perfect performance. The scores are then calculated for a total CAARV score as an aggregate of the scores of all four sub-tests.

**Table 2 Tab2:** Compressed Assessment of Ability Related to Vision (CAARV)

1. Computerized motion detection
A large black cross against a white background on a computer screen provides a point of fixation. While fixating on the cross, one at a time, 14 balls of different sizes and colors move diagonally across the screen from either the right or the left side at a constant speed. Yellow, red, or blue balls are used. The patient is asked to count the number of moving balls. Each ball seen counts as ½ point. Highest score is 7 and lowest score is 0.
2. Facial expression recognition

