Seven full-face professional, colored photos of varying sizes and facial expressions (angry, sad, happy, or surprised) are presented on a computer screen at a distance of ½ meter. The patient receives one point for recognizing the facial expression. Score ranged from 0 to 7 with 7 being the highest score.
3. Recognizing street signs
Seven written word signs ranging from large to small are read at a distance of 4 meters. One character in each sign was changed from familiar phrases making the word difficult to guess. For example, the top sign reads SUGAR DANE, which is similar to the more familiar sugar cane. The patient is instructed not to guess. One point is given for each sign read correctly. Highest score is 7 and lowest score is 0.
4. Locating objects
Fourteen red and beige boxes of different sizes are scattered around the testing room (4 x 2 meters). Sample boxes are shown before test started. The patient attempts to locate the boxes while seated. Each box found is worth ½ point. Highest score is 7 and lowest 0.

The NEI-VFQ-25 includes a series of 25 questions pertaining to vision or feelings about a vision condition (Table 3). The patients select answers among a multiple-choice list of possible responses. The values of these answers are re-coded and converted to a 0 to 100 scale so that the lowest and highest possible scores are set at 0 and 100. Researchers average together the items within each subscale to create 12 subscale scores and can calculate an overall composite score by averaging the subscale scores, excluding the general-health-rating question [28].

**Table 3 Tab3:** National Eye Institute Visual Functioning Questionnaire – 25 (NEI-VFQ-25)

1. In general, would you say that your overall health is:	
1) Excellent 2) Very Good 3) Good 4) Fair 5) Poor	
2. At the present time, would you say your eyesight using both eyes (with glasses or contact lenses, if you wear them) is:	
1) Excellent 2) Good 3) Fair 4) Very Poor 5) Completely Blind	
3. How much of the time do you worry about your eyesight?	
1) None of the time 2) A little of the time 3) Some of the time 4) Most of the time 5) All of the time	
4. How much pain or discomfort have you had in and around your eyes (for example, burning, itching, or aching)? Would you say it is:	
1) None 2) Mild 3) Moderate 4) Severe 5) Very severe	
PART 2 – Difficulty with Activities	

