18. Are you limited in how long you can work or do other activities because of your vision?	
19. How much does pain or discomfort in or around your eyes, for example, burning, itching or aching, keep you from doing what you’d like to be doing?	
For each of the following statements, please tell me if it is 1) definitely true, 2) mostly true, 3) mostly false, or 4) definitely false for you or you are 5) not sure.	
20. I stay home most of the time because of my eyesight.	
21. I feel frustrated a lot of the time because of my eyesight.	
22. I have much less control over what I do, because of my eyesight.	
23. Because of my eyesight, I have to rely too much on what other people tell me.	
24. I worry about doing things that will embarrass myself or others, because of my eyesight.	
25. I need a lot of help from others because of my eyesight.	

The study also uses a modified glaucoma symptom scale (MGSS), which includes 10 ocular complaints often associated with glaucoma or treatment for glaucoma (Table 4) [29]. For each eye, an initial four-level score is generated, with one signifying a very bothersome problem and four signifying the absence of a problem. This score is converted to a 0 to 100 scale, 0 signifying the presence of a very bothersome problem and 100 signifying the absence of a problem [29]. The final MGSS score is an unweighted average of the responses to all 10 items, averaged between the two eyes.

**Table 4 Tab4:** Modified glaucoma symptom scale

Have you experienced any of the following problems in the last 4 weeks?			
(Please respond for both the left and right eye.)			
a. Burning, Smarting, Stinging			
Left Eye		Right Eye	
☐ Yes	How bothersome has it been?	☐ Yes	How bothersome has it been?
	______ Very		______ Very
	______ Somewhat		______ Somewhat
	______ A Little		______ A Little
☐ No (Not at all bothersome)		☐ No (Not at all bothersome)	
b. Tearing			
c. Dryness			
d. Itching			
e. Soreness, Tiredness			
f. Blurry/Dim Vision			
g. Feeling of Something in Your Eye			
h. Hard to See in Daylight			
i. Hard to See in Dark Place			
j. Halos Around Lights			

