### Statistical analysis and sample size justification

*Primary Outcome Variables* will be divided into three groups: 1) QoL (NEI-VFQ-25 and MGSS) 2) performance-based measures of visual function (CAARV) and 3) Clinical measures of vision (better and worse eye VF mean defect, better and worse eye VA, and binocular SPARCS contrast sensitivity). *Primary Exposure/Demographic Variables* will be characterized as baseline DDLS score, age, ethnicity, gender, type of glaucoma, and number of medical comorbidities. *Secondary Variables* will be characterized as better and worse eye IOP, treatments, and duration of treatment.

All primary and secondary variables measured at baseline will be compared using means, medians, standard deviations, ranges or frequencies, and percentages. At baseline, Spearman correlation coefficients will be provided for all pairs of outcome variables and demographic variables.

In order to characterize the longitudinal trajectory of VRQoL, clinical measures of vision, and vision-related functioning over a 4-year period, analysis of these outcomes will proceed in two stages. First, mixed effects linear regression will be used to model the average trajectory of the sample. This will identify the appropriate parametric forms for each outcome trajectory. The study collects outcomes at five different timepoints over the 4-year study period. Linear and quadratic curves will be calculated, as well as a saturated model that treats time as a categorical explanatory variable. This allows for estimation of the mean outcome score for each visit. The mixed effects model will account for correlation among repeated measurements from the same patient. Our goal in these analyses is to identify the most parsimonious model that adequately represents the shape of the outcome trajectory over time. Ideally, a linear model will be sufficient. It is possible, however, to imagine scenarios where a quadratic term may be required (e.g., initial decline followed by stabilization).

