Second, because glaucoma is a disease with much subject heterogeneity, there are likely to be patients that differ from others in their experienced trajectories. MPlus software will be used to implement Growth Curve Mixture Modeling (GCMM) [30, 31]. This will group patients into a finite number of latent classes characterized by differing outcome trajectories over time. The model contains two parts: 1) the outcome model (i.e., the shape of the trajectory within each class), which is a mixed effects linear regression model and 2) the class probability model, which links the probability of being in any class with baseline exposure and demographic variables through a logistic regression model. Results from the initial mixed effects linear regression analysis will guide selection of the trajectory shapes for the GCMM. Results from the logistic regression portion of the model will allow for identification of baseline characteristics associated with differing changes in outcomes over time. Models will be fit with up to five latent classes using the Bayesian Information Criterion (BIC) to select the best-fitting model [32].

In order to determine whether changes in VRQoL are associated with changes in clinical measures of vision and performance-based measures of visual function, an extension of GCMM will be used to model to simultaneously model multiple outcome trajectories and identify classes based on the joint consideration of multiple outcomes. This will jointly model the trajectories of the primary outcome variables [32]. The resulting classes will have differing trajectory shapes for each outcome. Based on these results, we will be able to characterize the ways in which these outcomes change concurrently over time and the baseline patient characteristics that are associated with differing trajectories.

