No sample size formulae exist for GCMM. A sufficient sample size of 160 patients was chosen in order to identify subgroups using the latent class analysis. The primary goal of this analysis is to estimate parameters of the trajectory in each class with appropriate precision. The precision of the confidence interval will be calculated for the class- and outcome-specific slopes, assuming that a linear model is sufficient to describe the trajectory of a particular outcome. Class sizes will vary based on outcome. For illustration, we estimated precision for class sizes of 20, 60, and 100. Each patient will have up to five observations. Assuming 5 % dropout per year, the average number of observations per patient is 4.5.

Table 5 shows the width of the confidence interval for the slopes for NEI-VFQ-25 Total Score and LogMAR VA. For reference, a slope of one would indicate a 12-unit change in the NEI-VFQ over 12 months. A slope of 0.01 for LogMAR would indicate a change of 0.12 units over 12 months. The calculations given in Table 5 assume an intra-subject correlation of 0.2. Higher values within subject correlation would result in less precision while lower correlation would result in increased precision.

**Table 5 Tab5:** Sample confidence intervals for slopes of NEI-VFQ-25 and visual acuity

Number of subjects per class	Effective Sample Size N*4.5/(1 + (4.5-1)*0.2)	Distance from slope estimate to the two-sided 95 % confidence limits for the class-specific slope	
		NEI-VFQ (Std. Dev = 17)	LogMAR VA (Std. Dev = 0.2)
20	53	+/− 0.28	+/− 0.0033
60	159	+/− 0.16	+/− 0.0019
100	265	+/− 0.12	+/− 0.0014

*NEI-VFQ-25* National eye instate vision function questionnaire; LogMAR VA

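### For the three bounded primary scores, choosing the number of classes by BIC from normal linear growth mixtures can report spurious classes if the scores are skewed or pile up at their maximum, and no stated analysis would show it

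*Protocol article*

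**What the plan says.** The section on statistical analysis and sample size gives the growth curve mixture model (GCMM) two parts. The first is "the outcome model (i.e., the shape of the trajectory within each class), which is a mixed effects linear regression model". The second is a logistic model that links class membership to baseline characteristics. The number of classes is settled in one sentence: "Models will be fit with up to five latent classes using the Bayesian Information Criterion (BIC) to select the best-fitting model". No other criterion is named.

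The section on research instruments defines the three scores:
- NEI-VFQ-25 is "converted to a 0 to 100 scale so that the lowest and highest possible scores are set at 0 and 100".
- MGSS is on a 0 to 100 scale, "0 signifying the presence of a very bothersome problem and 100 signifying the absence of a problem", averaged over ten items and two eyes.
- CAARV has four sub-tests: "Each item is scored from 0 to 7, 7 being perfect performance". Its total therefore runs from 0 to 4 × 7 = 28.

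All three are primary outcomes. The other five are "better and worse eye VF mean defect, better and worse eye VA, and binocular SPARCS contrast sensitivity", for which no such bound is given. A later extension of the GCMM models the primary outcomes jointly.

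The first-stage mixed model compares linear, quadratic and categorical time. The one sensitivity analysis, under missing data, refits the final models in patients seen at every visit.

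**The concern.** A linear mixed model within class implies normal random effects and residuals. If a score is left-skewed or stops at a maximum, a single normal component fits badly. Adding a second component with a different mean improves the likelihood even when there is only one kind of patient. BIC then compares one misspecified model with another and may prefer the larger.

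The stated analyses would not reveal this. The first stage tests the shape of the mean over time, not the distribution around it. The completers analysis addresses missing data. Baseline medians and ranges would show a marked ceiling, but the article attaches no consequence to them.

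The sample size was chosen so that subgroups could be identified, and baseline predictors are to be attached to the classes. A class that only separates patients near the maximum from the rest would be reported as a patient type with its own course and its own predictors.

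**Working it through.** **The plan's own figures.** Table 5 reproduces. Average observations per patient: (1 + 0.95 + 0.90 + 0.85 + 0.80) = 4.5. Effective sample size: N × 4.5 / (1 + 3.5 × 0.2), giving 52.9, 158.8 and 264.7 for N = 20, 60 and 100 (stated: 53, 159, 265). Half-width: t × SD / (SD of time × √ESS), with SD of time 16.97 months for visits at 0, 12, 24, 36 and 48. For NEI-VFQ-25 this gives 0.276, 0.157 and 0.121 (stated: 0.28, 0.16, 0.12). For LogMAR it gives 0.00325, 0.00185 and 0.00143 (stated: 0.0033, 0.0019, 0.0014). The SD of 17 and correlation of 0.2 used below are therefore the plan's own inputs.

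**Does SD 17 fit under a maximum of 100?** A normal score with mean m lies above 100 with probability P(Z > (100 − m)/17). The means are assumptions:
- m = 66: z = 2.00, about 2%
- m = 75: z = 1.47, about 7%
- m = 80: z = 1.18, about 12%
- m = 85: z = 0.88, about 19%

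So the normal model is harmless in this respect for a mean in the 60s and strained for a mean in the 80s.

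**Simulation.** From the article: 160 patients, five visits at 0 to 48 months, SD 17, correlation 0.2. Assumed: correlations 0.5 and 0.8, the means, a mean slope of −0.05 per month with SD 0.08, and complete data. Every sample comes from one homogeneous population, so any second class is false. Normal linear growth mixtures with one to four classes and class-invariant variances were fitted, and the lowest BIC = −2 log L + p × ln(160) was chosen. Each extra class adds three parameters (intercept, slope, proportion), a penalty of 3 × 5.08 = 15.2, so a second class needs a log-likelihood gain above 7.6. There were 100 samples per cell (standard error up to 5 points). Ranges cover two versions: random intercept only, and random intercept and slope.

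Share of samples in which BIC chose more than one class:

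| Data | Assumed mean | At maximum | Corr. 0.2 | Corr. 0.5 | Corr. 0.8 |
|---|---|---|---|---|---|
| Unbounded normal | 85 | none | 0–1% | 0% | 0–1% |
| Capped at 100 | 75 | 6% | 0–2% | 1% | 3% |
| Capped at 100 | 80 | 11% | 1–3% | 6–8% | 23–29% |
| Capped at 100 | 85 | 17% | 8% | 41–44% | 64–76% |
| Capped at 100 | 90 | 26% | 31–34% | 81–87% | 100% |
| Smooth left skew (beta) | 75 | 0% | 12–17% | 38–51% | 74–88% |
| Smooth left skew (beta) | 80 | 0% | 41–48% | 83–93% | 99–100% |
| Smooth left skew (beta) | 85 | 0% | 89% | 100% | 100% |

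For the capped rows, the mean is that of the score before capping.

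A separate smaller simulation (30 samples per cell) gave 0% without a cap and 0–10% with 6–11% at the maximum. With 17% at the maximum it gave 13% at correlation 0.2 and 60–77% at 0.5–0.7. With 26% it gave 53–90%.

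In the capped cells with 17–26% at the maximum, the smaller class of the two-class fit held about 19–28% of patients: 0.19 × 160 = 30 to 0.28 × 160 = 45. That lies between the class sizes of 20 and 60 illustrated in Table 5, so such a class would not look too small to believe.

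**The case against.** The strongest objection is that the article documents bounded scales, not a ceiling effect. It gives no mean, no share at the maximum and no measure of skew, and it describes moderate-stage patients with field loss. An exact maximum on any of these scores needs a perfect result on every contributing item, so 17–26% at the maximum may be too many. At the plan's correlation of 0.2 with 6–11% at the maximum, the rule is nearly sound. This stands, and it is why the size can only be stated conditionally. It does not remove the point, for two reasons. Smooth left skew with nobody at the maximum also produces false classes. And 0.2 is a planning value; the article itself considers higher correlations.

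A second objection is that distribution checks belong in a full analysis plan, which is not shown. Their absence alone would indeed be no finding. But the article states the within-class model and the rule for the class count, and that combination can give a wrong answer.

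A reader might infer that the rule will invent classes in this cohort, that BIC is at fault, or that all primary outcomes are affected. The documents support none of these. The simulated rates run from 0% to 100% depending on undocumented quantities. BIC kept one class in 99–100% of unbounded normal samples. Five of the eight primary outcomes fall outside the argument. The three scores do enter the joint model, but no joint model was simulated.

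Nor does the argument require a censored (tobit) model as the primary analysis. Censoring does not describe smooth skew, and the BIC of a censored model is not comparable with that of a normal or skewed-density model.

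**Conclusion.** The concern holds in conditional form, for NEI-VFQ-25, MGSS and CAARV. Under homogeneity, with 160 patients and SD 17:
- about 0–3% false classes with 6–11% of scores at the maximum and correlation 0.2;
- about 8–13% with 17%, and 30–50% with 26%, at the same correlation;
- about 40–100% with 17–26% at the maximum and correlation 0.5–0.8;
- 0–1% with unbounded normal data.

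These figures rest on assumed means and slopes, on common variances across classes, on no dropout, and on a class model without covariates. They show what the rule can do, not what it will do here. Confidence in the mechanism is high. Confidence that it matters in this cohort is moderate at best, since the article does not give the score distributions that would decide it.

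**What to change.** Keep the normal GCMM as planned. For NEI-VFQ-25, MGSS and CAARV, prespecify a sensitivity analysis that repeats the class count with a non-normal within-class model: censored if the scores pile up at the maximum, skewed-distribution if they are smoothly skewed. Settle which applies from the pooled distribution of each score before any class model is fitted. Compare K classes with one class by BIC only within the same model family.

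Report the classes as patient subgroups only if more than one class is also supported there. Otherwise describe them as possibly reflecting the distribution of the score.

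The cost is a paragraph of analysis-plan text and extra analysis time, with no new patients, visits or measurements. The downside is that fewer classes may be reported. How well the added analysis restrains false classes was not simulated.

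### The growth mixture model's class-membership coefficients are read as predictors of change, but they test association with starting level or slope

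*Protocol article*

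**What the plan says.** All of this is in the protocol article, section *Statistical analysis and sample size justification*.

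- **Stage 1.** "mixed effects linear regression will be used to model the average trajectory of the sample". Its purpose is to choose the shape of each outcome's curve. No baseline characteristic, and no characteristic-by-time term, is described.
- **Stage 2.** A GCMM groups patients into one to five latent classes by their trajectories, with the number chosen by BIC. The within-class outcome model is a mixed effects regression. The second part is a class probability model, "which links the probability of being in any class with baseline exposure and demographic variables through a logistic regression model".
- **Interpretation.** "Results from the logistic regression portion of the model will allow for identification of baseline characteristics associated with differing changes in outcomes over time".
- **Joint model.** The later paragraph on several outcomes speaks of characteristics linked to trajectories, a looser and more defensible wording.
- **Sample size.** "A sufficient sample size of 160 patients was chosen in order to identify subgroups using the latent class analysis". Table 5 gives the precision of class-specific slopes. No figure is given for detecting a predictor of slope.

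**The concern.** The question is who changes differently. The stated test is whether a characteristic is related to class. Nothing described gives the classes a common starting level or lets a characteristic act on level within a class. A characteristic that goes with a worse starting value but the same rate of decline can therefore be accommodated only through class membership. The fit can separate classes by level, give the characteristic a significant class coefficient, and so have it reported as linked to differing change.

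Baseline disc damage score, age and comorbidity count could plausibly relate to the level of visual field, acuity, CAARV or NEI-VFQ-25. At stake is one of the study's main conclusions: which baseline characteristics go with faster or slower decline.

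**Working it through.** **1. Table 5 reproduced.** Inputs from the article: SD 17 (NEI-VFQ-25), mean 4.5 observations, intra-subject correlation (ICC) 0.2, visits at 0, 12, 24, 36 and 48 months (population SD 16.97 months).

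Effective N = N × 4.5 / (1 + 3.5 × 0.2) = 52.9, 158.8 and 264.7 for classes of 20, 60 and 100 (printed: 53, 159, 265).

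Half-width = q × 17 / (16.97 × √effective N), with q the t quantile, = 0.276, 0.157 and 0.121 per month (printed: 0.28, 0.16, 0.12). The inputs are therefore read as the authors meant them.

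**2. What the class coefficient tests.** Take two classes with intercepts a₁, a₂ and slopes b₁, b₂, and let p(x) be the probability of class 1 given characteristic x. If x enters only through p(x), the mean outcome at time t changes with x by

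p′(x) × [(a₁ − a₂) + t × (b₁ − b₂)].

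If a₁ ≠ a₂ and b₁ = b₂, the class coefficient is non-zero while x has no relation to change. A zero coefficient means no relation to level and none to slope. That is a different null hypothesis from no relation to change.

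**3. How often it matters: characteristic related to level only.** Two simulations, five annual visits, complete data. The correlations with level (r), ICCs above 0.2, random-slope sizes and slope effects are assumptions.

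- *A:* N=161, normal data, within-class random intercept and slope, one or two classes by BIC, likelihood-ratio test of the covariate. 100 replicates for r=0.3 and 0.5 at ICC 0.5 and 0.7; 40 to 60 elsewhere.
- *B:* N=160, total SD 17, random-slope SD 1.5 points/year, one to five classes by BIC, 100 replicates, three within-class structures.

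Share of trials in which the level-only characteristic is significant in the class model (one class chosen counts as not found):

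| ICC, r | A | B: random intercept | B: random intercept + slope | B: no random effect |
|---|---|---|---|---|
| 0.2, 0.3 | 15% | – | – | – |
| 0.2, 0.5 | 67% | 65% | 63% | 100% |
| 0.5, 0.3 | 27% | – | – | – |
| 0.5, 0.5 | 95% | – | – | – |
| 0.7, 0.3 | 36% | 32% | 32% | 86% |
| 0.7, 0.5 | 99% | 99% | 99% | 100% |

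The direct characteristic-by-time test rejected in 5–8% (A) and 7–9% (B), against a nominal 5%. With eight covariate terms, A gave 45% (one covariate at r=0.5, ICC 0.7) and 88–92% (three covariates at r=0.4, 0.4 and 0.3, ICC 0.5–0.7).

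**4. Is the level link the cause?** With r=0, A never chose two classes. In B, an unrelated covariate was flagged in 0–1% of trials with random effects. When A gave the covariate a direct effect on the intercept (ICC 0.5, r=0.3 and 0.5), two classes were chosen in 0%.

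**5. How large are the assumed links?** In A, r is the correlation with the patient's true level. The single-visit correlation is r × √ICC: 0.5 × √0.2 = 0.22, and 0.3 × √0.7 = 0.25. These are modest.

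**6. What the spurious classes look like.** In B (ICC 0.7, r=0.5, random effects) the classes differed by about 18 points at baseline (18/17 ≈ 1.1 SD) but by only 0.6–0.8 points/year in slope. From Table 5, the half-widths for classes of 60 and 100 are 0.16 × 12 = 1.9 and 0.12 × 12 = 1.4 points/year. For the difference between them the half-width is √(1.92² + 1.44²) = 2.4 points/year. On the plan's own precision these slopes cannot be told apart.

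**7. Characteristic related to slope only** (B, normal levels; share detected, range over the three structures):

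| Effect per SD | ICC | Class model | Direct test |
|---|---|---|---|
| 0.8 points/year | 0.2 | 8–49% | 59% |
| 0.8 points/year | 0.7 | 19–39% | 84% |
| 1.2 points/year | 0.2 | 49–81% | 85% |
| 1.2 points/year | 0.7 | 43–88% | 100% |

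A gives 15% against 80% at 0.05 SD/year (0.05 × 17 = 0.85 points/year) and ICC 0.5. With two true slope classes (0 and −5 points/year, odds ratio 2.7 per SD), B gives 15–56% against 48% at ICC 0.2, and 32–83% against 79% at ICC 0.7. The 83% is the random-intercept model.

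**The case against.** - **The plan produces what is needed to see the artefact.** It reports class-specific slopes with confidence intervals, and baseline Spearman correlations among outcomes and demographics. A careful reader would notice classes that differ in level with overlapping slopes. This stands as a safeguard, but it does not alter the stated rule that the logistic part identifies predictors of change.
- **A condensed article's silence is not exclusion.** It does not say that characteristics are barred from the within-class model, nor that classes differ in starting level. The latter follows only because nothing described constrains them. A reader might infer that the full plan has no direct effects or interaction terms; the article does not support that. The point rests on the inference the article does state. The random-effects structure, which a full plan might fix, does not rescue it: all three structures show the problem.
- **A reader might infer that a true predictor of slope would mostly be missed, so that the findings would be wrong in both directions.** That goes too far. Effects of 1.2 points/year were found in 43–88% of trials, and with true slope classes at ICC 0.7 the random-intercept model matched the direct test (83% against 79%). True subgroups are the setting the authors have in mind.
- **A reader might infer that false attribution is the rule.** It is conditional. The article gives no correlation between any characteristic and level, and restricting disc damage stage to 5 through 8 may weaken that one. At the article's ICC of 0.2 and r=0.3 the rate was 15%.

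**Conclusion.** The point holds as a mismatch between the stated model and the stated inference. As described, class coefficients address association with trajectory class, which mixes level and slope, and no described analysis tests a characteristic against change alone.

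With the within-class random effects that the article's mixed model implies, the false-attribution rate for a level-only characteristic ran from about 15% to 99%, and the assumed r and ICC decide where in that range it falls. Loss of power is shown for a moderate linear slope effect, not in general.

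Other limits: the simulations use complete data, whereas the article expects 4.5 observations per patient on average; most use a single continuous covariate; Monte Carlo error is up to about 5 percentage points with 100 replicates (√(0.25/100)) and about 8 with 40 (√(0.25/40)). This should be changed before analysis, but it does not invalidate the GCMM as a description of subgroups.

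**What to change.** 1. Keep the GCMM, but make the test of which baseline characteristics go with differing change the characteristic-by-time term in the stage 1 mixed model, with each characteristic's main effect on level and a random intercept and slope.
2. Describe class-membership coefficients as predictors of trajectory class (level and slope). Call them predictors of change only where the class slopes differ.
3. As a supporting GCMM, allow the baseline characteristics a direct effect on the within-class intercept, which Mplus can fit.

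The cost is some rewording and a few model lines, with no new data or patients. The downside is a few more parameters and possibly fewer classes to report.
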